#### Sample size estimate

An average medium effect size (Cohen *d* = 0.54) of PA intervention on FMSs in obese children was proposed based on previous studies [32]. Considering the minimal class size is 30 and the prevalence rate of childhood obesity is approximately 20% [60], a cluster size of 6 (for each class) was selected in this study. Using an ICC of 0.01 [61], an alpha of 0.05, a statistic power of 80%, and an attrition rate of 15% [43], at least 84 participants in each condition (12 clusters per condition), for a total of 168 participants in 24 clusters will be required for this CRCT.

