**Implementation**	Pilot study & Main study	1. Is the intervention delivered as intended? ● Using a process evaluation framework to assess the fidelity and quality of intervention implementation (e.g., exercise intensity will be monitored during the intervention; a fidelity evaluation scale will be used) ● Trained research staff observe teachers’ implementation of the FMSPPOC program (e.g., percent of lesson content conveyed, whether lessons will be presented in recommended order) and parents’ involvement in the family-based PA assignments ● Using self-reported e-logs to assess the participants’ satisfaction with the intervention implementation ● Using a self-reported scoring sheet to assess the consistency in delivering the intervention and evaluate the consistent commitment of facilitators and collaborators	1. Identify the acceptability, adaptability, and practicality of the intervention 2. Identify any modifications that have been done during the intervention process, and explore the reasons behind them 3. Identify the barriers that influence the fidelity of the intervention 4. Identify the potential facilitators and barriers that influence the intervention implementation and provide strategies to address them in the future
		2. Did participants adhere to the intervention program? ● Analyses for the attendance rate of each session and overall completion rate ● Check the completion of the family-based PA assignment by self-reported e-logs ● Self-reported e-logs completed by the intervention facilitators and collaborators	
**Maintenance**	Main study & Follow-up	1. The extent to which the intervention outcomes are sustained ● Data analyses for the sustained intervention effects during 6-month follow-up	1. Identify the components that influence the successful sustainability of the current program 2. Identify the modifications made to sustain the current program 3. Identify the facilitators and barriers of seeking more collaborators in future 4. Identify the facilitators and barriers that maintain the program and promote the program to a wider population in future

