### Outcome evaluation

A description of the measurements in the present study are presented in Table 4. All the measurements will be conducted on four occasions, including baseline assessment (T0), mid-intervention assessment (T1: 12 weeks after the baseline assessment), post-intervention assessment (T2: 24 weeks after the baseline assessment), and follow-up assessment (T3: 6-month after the intervention completion).

**Table 4 Tab4:** Description of the outcome measures

Outcomes	Measurement instrument

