### Data analysis

Quantitative data analyses will be performed using SPSS and Mplus. Descriptive statistics of all continuous variables will be expressed as mean ± standard deviation (*M* ± *SD*). Independent samples *t*-tests and Chi-square tests will be employed for checking the randomization, analyzing the dropout, and detecting the potential confounders at baseline. Intention-to-treat approach will be used for the primary analyses, with per-protocol analyses as sensitivity tests. Missing data will be imputed using a multiple imputation approach with linear and logistic regression equations. The statistical significance level will be set to *p* < 0.05 (two-tailed). Generalized linear mixed models (GLMM) will be used to evaluate the intervention effects on outcome measures, with time, condition, and the interaction of time and condition as fixed effects, adjusting for baseline values. Post-hoc tests will be conducted where a significant interaction effect is detected by using the least significant difference method. In addition, structural equation modeling will be used to analyze the interrelationship (e.g., mediation mechanisms) of outcomes, using a bias-corrected bootstrap approach (5000 resamples). For the qualitative data, a thematic analysis approach will be applied using NVivo 11 software.

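### Visit-specific contrasts are run only after a significant time-by-condition interaction, so in a baseline-adjusted model the T2 and T3 contrasts are withheld when the effect is stable

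*Protocol article*

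**What the plan says.** The Data analysis section of the protocol article gives one model for all outcomes: "Generalized linear mixed models (GLMM) will be used to evaluate the intervention effects on outcome measures". The terms of that model are specified in the same sentence: "with time, condition, and the interaction of time and condition as fixed effects, adjusting for baseline values". The sentence after it sets the rule for going further: "Post-hoc tests will be conducted where a significant interaction effect is detected by using the least significant difference method". The two-sided significance level is 0.05.

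The Outcome evaluation section lists four occasions: T0 (baseline), T1 (12 weeks), T2 (24 weeks, end of intervention) and T3 (six months after the intervention ends). The Data analysis section does not say whether T0 is also a level of the time factor, or which model term answers the primary question.

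Persistence of benefit is a declared target. The Maintenance row of the RE-AIM table (Implementation evaluation) lists "Data analyses for the sustained intervention effects during 6-month follow-up". The second half of the programme is a maintenance phase, and the Introduction faults earlier programmes whose gains were lost at follow-up.

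**The concern.** Baseline adjustment normally means that T0 enters as a covariate and the repeated outcomes are T1, T2 and T3. In that model the treatment effect sits in the condition term, or in the condition contrast at each visit. The time-by-condition interaction tests something narrower: whether the effect changes between T1, T2 and T3.

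Using that interaction as the gate to the visit-specific contrasts therefore works against the trial's own questions. A programme that works by week 12 and holds its effect has no interaction, so the rule stops the analyst from testing the difference at the end of the intervention (T2) and at follow-up (T3). A programme whose effect fades is more likely to pass. What is at stake is whether the trial can report, under its own plan, an effect at T2 and a sustained effect at T3 for the primary outcome.

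**Working it through.** **Inputs**

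- Effect size d = 0.54, 84 children and 12 classes per condition, class size 6, ICC 0.01, attrition 15% (Sample size estimate).
- Two-sided alpha 0.05; model terms and gate (Data analysis).
- Correlation ρ between a child's repeated measurements: not stated. Assumed to be 0.5 or 0.7, equal between all visits, with SD 1.

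**The plan's own sample size.** The simple formula gives 54 per arm; 54 × 1.05 / 0.85 = 66.7, or 72 in whole classes of six. The stated 84 can be reached in other ways: a class-level t-test needs 11 classes of 6 = 66 (power 0.821), and 66 / 0.85 = 77.6, which rounds up to 12 classes of 7 = 84. The present point does not depend on this. With 15% attrition, 84 × 0.85 = 71.4, so n = 71 completers per arm are used below.

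**Power of the gate.** Let δ_j be the effect at visit j and δ̄ its mean over the k visits in the time factor. A baseline covariate, and a class effect that is constant over visits, cancel from within-child differences. The interaction F-test then has (k − 1) and (2n − 2)(k − 1) degrees of freedom and noncentrality

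λ = (n/2) × Σ(δ_j − δ̄)² / (1 − ρ).

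Example, effects 0.54 / 0.54 / 0.27: δ̄ = 0.45; Σ = 0.09² + 0.09² + 0.18² = 0.0486; λ = 35.5 × 0.0486 / 0.5 = 3.45 for ρ = 0.5, and 35.5 × 0.0486 / 0.3 = 5.75 for ρ = 0.7. With 2 and 280 df the power is 36% and 56%.

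A simulation of 4,000 trials per scenario (71 per arm, 12 classes per arm, ICC 0.01) agrees. In the table, the first figure is for ρ = 0.5 and the second for ρ = 0.7.

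| Effect at T1 / T2 / T3 | Gate opens, formula | Gate opens, simulated | Condition term significant, simulated |
|---|---|---|---|
| 0.54 / 0.54 / 0.54 | 5% / 5% | 5.2% / 5.1% | 99.8% / 100% |
| 0.54 / 0.54 / 0.27 | 36% / 56% | 35.5% / 55.4% | 97.9% / 99.8% |
| 0.30 / 0.54 / 0.54 | 29% / 46% | 28.6% / 46.4% | 97.7% / 99.5% |
| 0.54 / 0.54 / 0 | 92% / 99% | 91.5% / 99.3% | 88.4% / 95.7% |

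For the constant effect Σ = 0, so λ = 0 and the gate opens only at the alpha level. It opens almost always when the effect has vanished by T3.

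**What is withheld.** For a direct baseline-adjusted contrast at T2 with independent children, SE = √[(2/71)(1 − ρ²)], which is 0.145 for ρ = 0.5 and 0.120 for ρ = 0.7. Then 0.54 / SE is 3.7 or 4.5, and the power is about 96% or 99%.

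**If T0 is also a level of time.** The effects are 0 / 0.54 / 0.54 / 0.54: δ̄ = 0.405; Σ = 0.405² + 3 × 0.135² = 0.2187; λ = 15.5 or 25.9 with 3 and 420 df. Power is 92% or 99% (simulated 92.2% / 99.5%), so the gate then does respond to a stable effect. But the T0 outcome is its own covariate. If the true baseline slope is 0.6 at T1–T3, the common fitted slope is (1 + 3 × 0.6) / 4 = 0.70.

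**The case against.** **Condition is in the model.** A reader might infer that the plan would miss a sustained effect altogether. The documents do not support that. Condition is a listed fixed effect, the gate applies only to post-hoc tests, and nothing says that the condition term will be ignored. In the simulation that term detects the constant effect in at least 99.8% of runs. This objection stands: what the rule withholds is the visit-specific result. But the condition term averages over T1, T2 and T3, so on its own it does not answer whether there is an effect at T2 or whether it persists at T3.

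**T0 may be a level of time.** Four occasions are defined and the text does not exclude T0 from the time factor. On that reading, gating on the interaction is a conventional repeated-measures rule and the failure described here disappears. The harm from having baseline on both sides should not be overstated either: with complete, balanced data a covariate that is fixed within a child leaves the time-by-condition estimates unchanged, and in simulation the T2 effect stayed at 0.53–0.55 against a true 0.54. Yet the stated baseline adjustment then does nothing for the interaction, which reduces to a comparison of changes from baseline. The wording fits T0 as covariate better, but does not settle it.

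**The gate limits multiplicity.** An overall test before unadjusted least-significant-difference comparisons is a familiar safeguard. That purpose is fair, but one pre-specified deciding test serves it without closing the door on a stable effect.

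**Detail may sit in an unseen analysis plan.** Contrast definitions can be left to that document. The gate, however, is a rule stated here.

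**Conclusion.** The point holds in a limited form and is a should-fix. On the natural reading (T0 as covariate, T1–T3 as outcomes), the rule withholds the T2 and T3 contrasts in about 95% of trials when the effect is constant. When it halves at T3 it withholds them in about 45–64% (100 minus 36–55). The result for a constant effect needs no assumption about ρ. The figures for near-stable effects rest on ρ of 0.5–0.7, equal correlation between visits and 71 completers per arm.

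Clustering was modelled by class, as in the sample size section, while the Randomization and blinding section allocates three schools per group. School-level analysis would lower the power of the condition term and of a direct T2 test, so the percentages for those should not be read as the trial's power. It would not make a constant effect show up as an interaction.

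The documents do not support saying that the intervention effect would go undetected, or that T2 must be the sole primary time point: the protocol names none, and T2 is one reasonable choice.

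**What to change.** Amend the Data analysis section to state that:

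1. T1, T2 and T3 are the outcomes, and T0 enters only as a covariate.
2. One baseline-adjusted between-condition test decides the primary question: either the difference at a named time point, such as T2, or the condition effect averaged over T1–T3.
3. That effect and the contrasts at T1, T2 and T3 are estimated from the model with 95% confidence intervals, whether or not the interaction is significant. Contrasts other than the deciding one are labelled supportive.
4. The interaction is used only to describe how the effect changes over time.

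The cost is a few sentences, settled before outcome data are analysed. No further data are needed. Removing the gate does not itself change the sample size.

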To address the research and practice gaps, the present study aims to develop, implement, and evaluate a 24-week school-family blended multi-component PA intervention program for promoting FMSs and health among Chinese obese children, namely Fundamental Motor Skills Promotion Program for Obese Children (FMSPPOC). The particular objectives of outcome evaluation include: (1) examine the intervention effects of the FMSPPOC on improving the primary outcome (i.e., FMSs) among Chinese obese children; (2) examine the intervention effects of the FMSPPOC on improving the secondary outcomes (health behaviors, physical fitness, perceived motor competence, perceived well-being, M-PAC components, anthropometric and body composition measures) among Chinese obese children; and (3) identify the interrelationships between FMSs and physical and psychological outcomes (i.e., mediation mechanisms) and the moderating role of demographics.

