#### Randomization and blinding

To avoid the potential for contamination, randomization will be conducted at the school level. All eligible schools will be randomly assigned to one of the two groups prior to baseline assessment, where each group will consist of three schools. Each school will select 28 obese children from four classes covering grades 2–5 to participate in this study, and the children in the same school will receive the same treatment. Randomization will be implemented with a ratio of 1:1, using the Excel software by a researcher who will not be involved in the participant recruitment, data collection or evaluation. Due the ethical concerns, participants are not able to be blinded as they will be informed with the study purpose and group allocation in the written informed consent form. Intervention facilitators and outcome evaluators will be concealed for the group allocation.

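### The bias-corrected bootstrap planned for mediation does not hold its 5% level for indirect effects that start from the randomised condition, whether children or the six schools are resampled

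*Protocol article*

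**What the plan says.** The third objective, at the end of the Introduction, is to "identify the interrelationships between FMSs and physical and psychological outcomes (i.e., mediation mechanisms". It stands beside the two objectives on intervention effects and carries no exploratory label. The preceding paragraph of the Introduction on research gaps says that earlier studies have not examined why such interventions improve motor skills, and treats finding the programme's own mediators as necessary.

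The Data analysis section gives the method in one sentence: structural equation modelling, "using a bias-corrected bootstrap approach (5000 resamples". It names neither a cluster level for the model nor the unit to be resampled.

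Under Randomization and blinding, "randomization will be conducted at the school level" and "each group will consist of three schools". The section adds "Each school will select 28 obese children from four classes covering grades 2–5". All children in a school receive the same treatment.

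The only ICC in the article is the 0.01 under Sample size estimate. There it is paired with classes, not schools: "a cluster size of 6 (for each class) was selected in this study".

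**The concern.** An indirect effect of the programme is the product of two paths: condition to mediator (a) and mediator to outcome (b). Condition varies only between schools, so path a is a contrast of three schools with three, however many children are measured. Resampling single children leaves the between-school variance out of the interval for a. Resampling schools has only three units per arm to draw from. The bias correction adds some anti-conservatism of its own.

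At stake are the claims about how the programme works, which the Discussion lists among the trial's strengths. A measure that the programme did not change could be reported as a mechanism more often than the nominal 5% implies.

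**Working it through.** The article gives no error rate or power for the mediation analysis, so there is no stated figure to reproduce.

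**Inputs from the article.** Six schools, 3 per arm; 28 children per school; 15% attrition, so about 28 × 0.85 ≈ 24 analysed; ICC 0.01; two-sided 5%.

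**Assumptions.** No effect of condition on the mediator (a = 0); b = 0.4; school ICCs of 0.05 and 0.10 shown as a range, because the article gives no school ICC.

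**Step 1: path a, children treated as independent.** The design effect is DE = 1 + (m − 1) × ICC, and the standard error is too small by √DE. The normal-theory type I error is 2 × [1 − Φ(1.96/√DE)]. With m = 28:

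| School ICC | DE | √DE | Type I error, path a |
|---|---|---|---|
| 0.01 | 1.27 | 1.13 | 8.2% |
| 0.05 | 2.35 | 1.53 | 20% |
| 0.10 | 3.70 | 1.92 | 31% |

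**Step 2: the indirect effect, children resampled.** Simulated rejection rates of the bias-corrected 95% interval for a × b:

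| School ICC | 24 per school, 1500 trials, 600 resamples | 28 per school, 1000 trials, 1000 resamples | 24 per school, 1000 trials, 600 resamples |
|---|---|---|---|
| 0 | 8.1% | 7.8% | 7.8% |
| 0.01 | 9.5% | 10.1% | 10.4% |
| 0.05 | 21.9% | 24.5% | 23% |
| 0.10 | 33.7% | 38.1% | 32% |

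A further repeat under the same effect assumptions gave about 7, 9, 23 and 30%. In the 28-child runs a plain percentile interval gave 5.8% at ICC 0 and 7.0% at 0.01. Much of the excess at the plan's ICC therefore comes from the bias correction. At ICC 0.05 and 0.10 the percentile interval also failed (22.4% and 34.8%), so there the cause is clustering.

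**Step 3: schools resampled within arm.** Three schools drawn with replacement give 10 distinct samples per arm, hence 10 × 10 = 100 in all, so 5000 resamples add nothing. Simulated rejection was 20, 19, 21 and 21% at ICC 0, 0.01, 0.05 and 0.10 (19–23% in the repeat).

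A rough calculation for path a agrees. Bootstrapping three units understates the variance by (3 − 1)/3 = 2/3, and a normal cut-off stands in for t on 4 df. The implied critical value is 1.96 × √(2/3) = 1.60, and P(|t₄| > 1.60) ≈ 18.5%.

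**Step 4: a method that uses the schools.** A school-level test of a on 4 df, combined with a b path estimated with school in the model, both required to be significant, gave 4.7, 4.3, 5.0 and 5.3% at the same four ICCs (about 3–7% in the repeat).

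**Step 5: where the problem is small.** Children resampled, bias-corrected interval:
- Predictor measured on the child, a = 0, b = 0.4: 7.9, 9.2, 9.6 and 12.2% at ICC 0, 0.01, 0.05 and 0.10 (percentile interval 5.9, 7.6, 7.0 and 9.7%).
- Condition does move the mediator (a = 0.54) but b = 0: 7.1–8.9%, with no clear trend in ICC.
- Both paths zero: about 1%.

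**The case against.** **The article is silent on the resampling unit, and silence is not a decision.** This stands. A reader might infer that the plan excludes a school level or has chosen to resample children. The article says neither, and a statistical analysis plan could name the unit or specify a multilevel model. But the article does fix the type of interval, and Steps 2 and 3 show that it misses 5% with children and with schools as the unit. Naming the unit later would not repair it; the interval would have to be replaced.

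**The objective concerns relations among outcomes, not effects of condition.** This stands in part. The objective's wording, and the motor-development model in the Discussion, describe child-level paths, for which Step 5 shows much less inflation. The Introduction also asks for the mechanisms of the intervention programme itself, and that needs a path from condition.

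**The size at the plan's own ICC is modest.** This stands. In the 1500-trial run, 9.5% against 8.1% is a difference of 1.4 points with a simulation standard error of about 1.0. All the runs point the same way, but a reader should not infer that missing clustering explains most of the excess at 0.01. The larger figures need school ICCs that the article does not give.

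**False mediators will be reported.** This is too strong. The inflation needs a null condition path together with a real mediator–outcome path.

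**Conclusion.** The point holds for indirect effects that start from the randomised condition. With a = 0 and an assumed b of 0.4, the stated interval rejects about 9–10% of the time at ICC 0.01 if children are resampled. About 7–8% of that is there without any clustering. The rate is about 22–25% at an assumed school ICC of 0.05 and 30–38% at 0.10. If schools are resampled it is about 20% at every ICC.

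The 0.01 is itself a value used for classes of 6, so it is no assurance about schools of 28. The documents do not support saying that a school level has been ruled out, or that every mediation interval will be badly narrow. Relations among child-level outcomes are much less affected, and the primary comparison is not affected. The method should still be changed, because mediation is a stated objective and the interval type is already fixed.

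**What to change.** For effects of condition through a mediator, replace the bias-corrected bootstrap:
- Estimate condition to mediator at school level, by a school random intercept or by school means, with t on 6 − 2 = 4 df.
- Estimate mediator to outcome within schools, from school-centred values. Do this in a separate model, since school as a fixed effect would absorb condition.
- Declare mediation only if both paths are significant. Alternatively, use a Monte Carlo product interval that draws the condition path from t with 4 df; normal draws would lose the small-sample correction. Only the joint-significance form was simulated here, so the Monte Carlo form should be checked before use.

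For paths among child-level outcomes, account for school and use a percentile interval in place of the bias-corrected one.

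Taking the mediator at T1 and the outcome at T2, and labelling the results exploratory, are optional.

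The change is a few lines of text and code. The price is precision. At ICC 0.01 and 28 children per school, the interval for condition to mediator is √1.27 × 2.776/1.96 = 1.127 × 1.416 ≈ 1.60 times the naive width, mostly because of the 4 df. If the programme shifted a mediator by 0.54 SD (the plan's effect size for motor skills, borrowed here), power for that path would be about 65% at ICC 0.01 and 41% at 0.05. Fewer mediators will be declared, and that is the limit of what six randomised schools can support.

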## Discussion

Obesity is becoming an increasing problem also in China and Chinese children, but rather little evidence is available how to address this. There are indicators, that this trend is similar to those in other countries. In 2008, Stodden et al. [33] proposed a “conceptual model of children's motor development” based on partial evidence and experience, which hypothesized the relationship between FMSs and multiple health indicators (e.g., PA, perceived motor competence, physical fitness, and weight status) of children. The authors point out that FMSs levels may positively or negatively affect PA and weight status in children, and that healthy or unhealthy weight status may also promote or restrict the development of FMSs in children over time, with perceived motor competence and physical fitness mediating the relationship between FMSs and PA [33]. In recent years, overweight and obese children have been consistently reported as scoring significantly lower than their healthy weight counterparts on FMSs, suggesting that poor FMSs can contribute to overweight/obesity [21–25, 94]. Similarly, obesity may likewise act as a constraint on FMS development and proficiency, generating biomechanical changes and adjustments in movement [94]. In previous studies, FMSs have been shown to correlate with PA in school-aged children [4], and strong positive associations have been observed between FMS proficiency in children at age 6 and leisure time PA in adults at age 26 [95]. Further to regular PA participation, additional health benefits of FMSs proficiency have been associated with increased cardiorespiratory fitness [96] and perceived motor competence [10, 14], as well as reduced overweight and obesity [12, 13]. This indicates the importance of effective interventions being implemented to allow overweight/obese children to develop their FMS early, reducing their risk of obesity through continued PA into adolescence and adulthood.

To our knowledge, FMSPPOC is the first school-family blended multi-component FMS-promotion program to be designed in China, which makes up the research and practical gaps as suggested in previous studies and shows a series of strengths: 1) standard methods will be applied for assessment of FMSs; 2) the use of theoretical framework and behavioral change techniques will ensure the implementation and effectiveness of the FMSs promotion program; 3) the gold standard for scientific designs (i.e., CRCT) will be applied and comprehensive measures will be implemented, which can contribute to a robust examination of the program effectiveness and a better understanding of the potential mechanisms; 4) the use of the RE-AIM framework will enhance the quality of the program and enable us to evaluate the implications of FMSPPOC among obese children broadly. We anticipate that FMSPPOC will also be a new paradigm of secondary obesity prevention. In addition, we will propose and assist health and education governments to advocate and disseminate the blended intervention among all primary schools to tackle unhealthy lifestyles in children and further improve health status of obese children in China. Other countries and regions with similar demographics to China can also learn and benefit from this product. Surely, comparisons to other cultures need to follow up and mechanisms are required to be evaluated, too. With that, the research of this study and comparable one can inform not only research and practice but also theory refinement and scaling up approaches.

